### Data collection and management

Participants will be required to attend the University Hospital Heidelberg on five occasions. All study visits will be planned, if possible, with routine care visits. All assessments will last between 1.5–2 h. Participants will be advised to wear comfortable shoes and clothes and to arrive hydrated to the study visit. Assessments will be done by study investigators, who have been extensively trained. Moreover, a number of pilot tests were performed prior to the study. To maintain high methodological quality, internal inspections of the methods will be carried out. Data will be collected and managed using REDCap electronic data capture tools hosted at the University Hospital Heidelberg. REDCap is a secure web application for building and managing databases developed at Vanderbilt University and launched in 2004 [99, 100]. Data will be entered digitally throughout each assessment using a mobile tablet. Only study investigators will have access to the REDCap project and will be able to do entries. The principal investigator and the study coordinator will have the right to unlock entries after assessment completion to do major adjustments. To assure high data quality, background validation has been installed for the majority of variables. Remaining variables will be checked for logic by study coordinator.

When participant attends the assessment, he/she will be asked to complete a survey using a mobile tablet. The survey includes sociodemographic questions, questions on fatigue, GvHD symptoms and on quality of life. Patients will receive immediate feedback when implausible values have been given, hence, responds can be adjusted. If assistance is needed, the study investigators will administer participants via interview. In case of tablet rejection, participant can respond on a paper-based questionnaire. After completion, physical assessments will be conducted, followed by the nutritional assessment. Patients will be contacted via telephone for the following assessment appointments.

Reasons for drop-out throughout the study will be recorded where possible. No further data will be collected in patients who withdrew from the study.

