## Methods/design

### Study design

The IRENE-G study is a 24-week prospective, randomized, controlled, intervention trial with a two-armed parallel design and 1:1 allocation ratio of GvHD patients treated with systemic steroids.

The study examines and compares the effects of a supervised resistance exercise intervention and a nutritional optimization program (experimental group) against a nutritional optimization program only (control group) on physical performance in GvHD patients treated with steroids. The investigators hypothesize that both groups will benefit with regard to physical performance after 24-weeks, however, the authors assume that the effect will be significantly greater in the experimental group compared to the control group. Moreover, the investigators hypothesize that the experimental group will have lower levels of fatigue, less perceived GvHD symptom burden, a higher perceived quality of life, better muscle strength values and a higher vastus lateralis muscle volume, a better nutritional status as well as a better submaximal endurance capacity compared to the control group.

The flow through the IRENE-G study is presented in Fig. 1. The research will be conducted at a single site (University Hospital Heidelberg, Germany). Upon written informed consent, eligible patients will be randomly assigned to the experimental or control group. Patients in the experimental group will take part in a 24-week supervised resistance exercise program and a nutritional optimization program. The moderate-to-high intensity resistance exercise sessions will be performed for a duration of 60 min two times a week. Patients in the control group receive nutritional optimization only. The interventions will start directly after the completion of the baseline measurements (t0). Further assessments will take place 8 weeks (t1), 16 weeks (t2), and 24 weeks (t3, primary endpoint assessment) after baseline assessment. A follow-up assessment (t4) is planned 48 weeks after baseline. All assessment points are embedded into medical care/ outpatient visits.

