### Sample size

To our knowledge no supervised, progressive moderate-to-high intensity resistance exercise study in a GvHD population treated with systemic steroids with the primary endpoint physical performance measured via the SPPB exists, as of yet. Consequently, the effect size for the primary outcome measure is unknown. The sample size calculation for the present exploratory project is based on a conservative estimation, using a mean standardized effect size of 0.5. To detect a corresponding effect with ANCOVA at a significance level of 5% with a power of 80%, 42 participants per group are required. Based on unpublished data of a previous study of ours, we expect a drop-out rate of 15% and a mortality rate of 10%. Consequently, 56 subjects per group need to be enrolled.

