### Intended statistical analysis

Data of the primary endpoint will be analyzed after study completion, no interim statistical analysis will be conducted. Descriptive statistics will be performed for sociodemographic and clinical variables measures at baseline for both arms. Absolute and relative frequencies will be used for categorical and the mean ± standard deviation (or median and range) will be used for continuous variables. In addition to descriptive evaluation procedures, inferential statistical methods will be used. The primary analysis will be based on an intention-to-treat principle. The authors will use ANCOVA to compare the SPPB changes from baseline to the end of the intervention between the two intervention arms. Standardized effect sizes with 95% confidence intervals will be calculated. For further exploratory analyses further model procedures (e.g. generalized estimating equation) and multiple regressions will be used. The significance level will be set at α = 0.05 (two-sided). Missing data will be dealt with using scoring manuals if present. When clinically and methodological reasonable, multiple imputation will be used. Adverse events will be evaluated descriptively based on the per-protocol population. Statistical analyses will be carried out in cooperation with the Institute for Medical Biometry at the University of Heidelberg. Access to the final dataset will be granted for the statistician and the principal investigators.

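### Intention-to-treat is declared but not secured: data collection ends at withdrawal, the primary ANCOVA uses only baseline and week 24, and imputation is discretionary

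*Protocol article*

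**What the plan says.** The Intended statistical analysis section states: "The primary analysis will be based on an intention-to-treat principle". It then fixes the model: "The authors will use ANCOVA to compare the SPPB changes from baseline to the end of the intervention between the two intervention arms". The Study design section places that assessment at "24 weeks (t3, primary endpoint assessment) after baseline assessment". Table 1 shows SPPB measured at all visits, t0 to t4, so values at weeks 8 and 16 will exist for many patients who later lack week 24.

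On incomplete data, the same analysis section offers two provisions: "Missing data will be dealt with using scoring manuals if present" and "When clinically and methodological reasonable, multiple imputation will be used". It gives no criterion for the second, no list of imputation inputs and no rule for patients who die. Longitudinal models appear only in this sentence: "For further exploratory analyses further model procedures (e.g. generalized estimating equation) and multiple regressions will be used".

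The Data collection and management section asks for drop-out reasons to be recorded where possible and then says "No further data will be collected in patients who withdrew from the study". It defines neither drop-out nor withdrawal. The Sample size section states "we expect a drop-out rate of 15% and a mortality rate of 10" per cent, and enrols 56 per group to retain 42.

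**The concern.** An intention-to-treat comparison needs either outcomes on everyone randomised or a committed way of handling those who have none. Here the first is limited by a conduct rule and the second is left open. If imputation is not judged reasonable, the ANCOVA runs on patients with a week-24 SPPB, and a patient measured at weeks 8 and 16 but not at week 24 drops out of the primary comparison.

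What is at stake is the randomised comparison. Only the experimental arm has twice-weekly training to tolerate, so patients doing poorly might leave that arm more often. In that case the remaining patients would flatter exercise. The direction and size depend on how drop-out operates, so the working below treats it as a scenario.

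**Working it through.** **Reproducing the plan's figures (Sample size section).** Inputs: 42 analysable per group, 15% drop-out, 10% mortality.

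- Additive losses: 42 / (1 − 0.25) = 56 per group, which is the stated number.
- Sequential losses: 42 / (0.85 × 0.90) = 54.9, so 55 per group, which is close.
- Expected without a week-24 SPPB: 112 × 0.25 = 28 patients. With sequential losses, 112 × (1 − 0.765) = 26.3, or 23.5%.
- Remaining: 112 − 28 = 84 = 2 × 42, the number on which the power rests.
- Split of the 28: drop-outs 112 × 0.15 = 16.8, about 17; deaths 112 × 0.10 = 11.2, about 11. Only the 17 could be reached by a different follow-up rule.

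**Size of a completer bias, by hand.** Let m1 and m0 be the proportions missing in the exercise and control arms. Let D1 and D0 be how much worse (in SD, after baseline adjustment) the missing patients would have been than the completers. Then

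bias of the completer contrast = D1 × m1 − D0 × m0.

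With m1 = m0 = 0.25 and D1 = D0, the bias is 0. With D0 = 0 and D1 = 0.25, it is 0.25 × 0.25 = 0.0625 SD. The document gives no value for D.

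**Size by simulation.** All settings except the 56 per group and the 0.5 SD effect are assumptions: correlations between visits of 0.60 to 0.75, about 19% to 24% missing at t3, and drop-out depending on poor SPPB at t1 or t2. Independent runs of 1,500 to 3,000 replicates agree.

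| Outcome-driven drop-out | True effect (SD) | Completer ANCOVA | Method using t1 and t2 |
|---|---|---|---|
| Exercise arm only | 0.50 | 0.55 to 0.56 | 0.50 |
| Exercise arm only | 0.00 | +0.065 to +0.075 | 0.00 |
| Both arms alike | 0.50 | 0.49 | not needed |
| Both arms alike | 0.00 | about 0.00 | not needed |

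The method using t1 and t2 was a likelihood analysis. Multiple imputation from t1 and t2 gave the same 0.50 and 0.00. A steeper one-arm drop-out relation moved the completer results to 0.59 and +0.11.

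**In proportion.** 0.05 / 0.5 = 10% and 0.07 / 0.5 = 14% of the planned effect. Against a standard error of about 0.165, 0.07 / 0.165 = 0.42, so the bias is under half a standard error.

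**Precision.** The SD of the estimate was 0.164 for the method using t1 and t2 and 0.168 for the completer ANCOVA, so using the earlier visits cost nothing.

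**The case against.** The strongest reply is that the protocol names multiple imputation next to an intention-to-treat declaration. That pairing is a standard way of keeping all randomised patients in a two-time-point ANCOVA, and SPPB at t1 and t2 can feed the imputation. This stands: a reader might infer that the plan prescribes a completer analysis, or that the t1 and t2 values are wasted, and the text supports neither. It also does not say when the decision to impute is taken, so a claim that it will be made after seeing open-label data is inference. The imputation model itself may properly be left to the analysis plan.

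Second, the data-collection rule covers withdrawal from the study. The Interventions section treats discontinuing an individual's intervention as its own decision, the Exercise intervention section covers temporary interruption, and the Recruitment section covers withdrawal of approval. No sentence says that a patient who stops training is no longer assessed, and that stronger reading should not be drawn. Equally, no sentence says that assessments continue, and the rule directly follows one about drop-out with both terms undefined.

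Third, nothing in the document shows that drop-out will be driven by outcome in one arm only. Deterioration and death affect both arms, and controls recruited as willing to train may leave too. This also stands, and it makes the bias conditional.

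The argument that a later analysis plan can settle everything does not stand. Such a plan can fix the model and the imputation, but it cannot recover week-24 measurements that were never taken.

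**Conclusion.** The point holds as a weakness in securing the intention-to-treat claim. It is not a demonstration that the primary result will be biased. Three features combine: an undefined boundary between stopping the intervention and withdrawing, a two-time-point primary model, and imputation without a commitment. About 25% of patients are expected to lack a week-24 SPPB.

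A completer ANCOVA would overstate the exercise effect by about 0.05 to 0.07 SD if outcome-related drop-out is concentrated in the exercise arm. With the same mechanism in both arms, the bias is close to zero. Both figures rest on the assumed correlations and drop-out model. The repair by t1 and t2 assumes that drop-out is explained by the observed SPPB values; loss that depends on the unseen week-24 value would not be fully corrected.

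Two further inferences should be resisted. The whole quarter is not recoverable by better follow-up, because about 11 of the 28 are deaths. Those need their own rule, which neither imputation nor a mixed model supplies. And the mention of generalized estimating equations does not damage the primary analysis. The unweighted form generally needs data missing completely at random, but it is named only as an example for exploratory work, so that point is secondary.

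**What to change.** 1. **Data collection and management section:** state that stopping training or nutritional therapy is not study withdrawal, and that the t1 to t4 assessments continue unless the patient withdraws consent to data collection. This is feasible because the assessments are tied to outpatient visits. It should be settled while patients are still in follow-up.
2. **Intended statistical analysis section:** commit the primary week-24 comparison to a method that uses SPPB at t1 and t2. Either of these serves: a mixed model for repeated measures adjusted for baseline SPPB and the stratification factors, with the week-24 contrast as primary; or the stated ANCOVA with mandatory multiple imputation from t1 and t2.
3. **Same section:** state how deaths before week 24 enter the primary analysis. A mixed model or imputation left to itself treats a patient who died as having an unobserved SPPB, and that should be a stated choice.

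The cost is wording in two sections and possibly a note in the patient information. Including patients who stopped training may slightly shrink the estimated effect. No extra patients or visits beyond those already scheduled are needed.

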### Data monitoring

A Data monitoring committee will not be included in this project as the trial involves behavioral interventions with known and especially minimal risks. Hence, no periodic benefit-risk assessment is needed. No independent auditing of study conduct is planned.

### Confidentiality

Confidentiality (with regard to the Federal Data Protection Act) of all patient-related data will be ensured, as all information will be pseudonymously (encrypted) and stored securely at the study site in areas with limited access. Moreover, access within the project team will be the minimum required for data analysis and quality control. A separate log relating original patient data with its respective, encrypted data will be created and appropriately secured by password; only authorized study personal will be granted access to this file.

### Interventions

Both study interventions (nutritional optimization as well as exercise training) will be delivered for a duration of 24 weeks followed by a 6 month follow-up phase. For both arms there are arrangements for ancillary or post-trial care. No special arrangements for compensation for those who suffered harm resulting from trial participation are taken. A decision to discontinue an individual’s intervention will be made jointly within the investigator team if there is concern that the intervention is causing harm. The overall study will be discontinued if the ethic committee decides to terminate the study. During the trial, no specific concomitant care or interventions are prohibited.

### Nutritional intervention

The nutritional status of participants of the control and of the experimental group will be examined at t0 using the NRS 2002, measurements of the hand grip dynamometer and medical/laboratory data which were collected during the latest clinical practice (e.g. weight, blood parameters like total protein, albumin, c-reactive protein, electrolytes as sodium, potassium, magnesium, phosphate, kidney and liver values, glucose, triglyceride). Based on participants individual needs and/or changes in general condition/nutritional status, nutritional recommendations are given. If malnutrition or a risk for malnutrition is detected, first step will always be oral supplementation, e.g. with protein supplements or oral nutritional supplements. In severe cases a nutritional therapy with e.g. enteral or parental infusion therapy will be initiated. Study participants will be contacted weekly to adapt nutritional therapy.

Throughout the study, nutritional recommendations and therapy will be adapted based on the risk of malnutrition (NRS 2002 score ≥ 3, low hand grip strength (men < 30 kg; women < 20 kg) defined as at least two standard deviations below the mean of the norm value, low serum albumin (< 30 g/l) and total protein (< 60 g/l)).

The main nutritional intervention is based on the scheme by Virizuela et al. [102] shown in Fig. 2. If the energy and protein level is below 75% of the previously defined requirement for a maximum of 7 days, a re-evaluation takes place and oral nutritional supplements may be used. If there is an indication for additional action such as enteral or parenteral nutrition, this will also be initiated. If enteral feeding via tube is refused by the patient or if the use of a tube is contraindicated from a medical point of view, parenteral nutrition will be started in consultation with the study patient and the physician. In addition to macronutrients, nutritional therapy always ensures an adequate supply of micronutrients. If study patients of both groups (experimental and control) still need nutritional therapy after intervention period, it will be ensured as part of the usual medical care system.

**Fig. 2 Fig2:**
[figure not shown]
Flow algorithm optimized nutritional medical care according to Virizuela et al. [102]

### Exercise intervention

Participants of the experimental group receive, in addition to nutritional endorsement, a supervised progressive moderate-to-high-intensity resistance training program. Depending on their medical condition and Covid-19 precautions and immune status patients have the opportunity to train live-online or at our exercise facility at the National Center for Tumor Diseases (NCT) or at certified training facilities near their home provided by the network OnkoAktiv.

Participants will be provided with an exercise intervention booklet. The booklet, written in plain language, contains educational information about physical exercise and cancer, information about the exercise intervention process, weekly physical activity logs and a catalogue with illustrated exercises (~ 15) for strengthening the muscles. Moreover, patients will receive stretch bands with different levels of tension. After the handover, the booklet will be discussed verbally with the participant by the study investigators, to ensure comprehension.

Regardless of the training location, participants will be supervised by an experienced exercise therapist or physiotherapist. Introductory training sessions will be scheduled before the start of the intervention program in order to screen the patients and to adapt the program in case of physical limitations. Each training session begins with a low-intensity warm-up (5–10 min stretching or mobility exercises), followed by the resistance training regime (45 min), and a cool-down (5–10 min) which will include stretching of major muscle groups. Online exercise session will be offered in small groups on weekday afternoons in order to ensure that participants who have medical appointments or other commitments are able to participate.

Exercise training is scheduled 2 times a week (separated by at least 48 h) for a total duration of 60 min. The program targets all major muscle groups, however, emphasis will be put on the lower extremities, as they are primarily affected by the GvHD treatment. The focus of the resistance training will be on muscle hypertrophy. The progressive program for participants who will train at facility centers comprises of 6–8 machine-based exercises, each performed in two sets, 12 repetitions at 60–80% of one repetition maximum (1-RM). For participants who train online, the individual training load will be defined during the introductory training session with the aim of choosing a load which to perform two times 12 repetitions. Patients will be coached in correct techniques for each exercise. Resting time between sets will be 1–2 min, and contractions will be performed at moderate velocities. The exercise intensity will be continuously adapted throughout the 24 weeks. The training is progressive in terms of weight increase to the next machine weight level (at least by 5%) after successfully completing two sets of an exercise with 12 repetitions in three consecutive exercise sessions. If deteriorations occur, the weights will be decreased, if two sets of an exercise within 12 repetitions in two consecutive exercise sessions cannot be attained. Participants will be contacted when 2 session in a row were not joined, without reasoning. Compliance with the exercise program will be determined via self-reported and objective measures such as attendance, exercise logs, target intensity.

Before and after each training session, participants will be asked to complete an exercise log. The physical activity log will be used for exercise monitoring and for adjusting. Moreover, it will be used as a measure of additional physical activity outside of the exercise intervention (such physical activity is not restricted or prohibited). Patients will be asked to report their perceived health status prior and after the training session as well as problem or symptom occurrence related to the exercise program. Further, the performed sets and repetition as well as the perceived exertion of each exercise and discomfort will be recorded. Every 4 weeks patients are instructed to drop off the logs during outpatient visit.

To promote retention patients will be contact weekly in the first 4 weeks and then every 2 weeks. Exercise sessions will temporarily be interrupted if severe pain, dizziness, nausea or other contraindication (thrombocytes ≤20.000/μl, hemoglobin ≤8.0 g/dl, fever (≥38,0 °C), severe infections, acute thrombosis or embolism, increased tendency to bleed) occur. When the study is complete, participants will be encourage to continue exercising in certified training facilities of the network OnkoAktiv or individually. Training protocol comply with the American College of Sports Medicine exercise guidelines for cancer survivors and with the American College of Sports Medicine recommendations for progressive resistance training for novice weightlifters and older adults for one to three sets at a weight that can be done/lifted for 8 to 12 repetitions (approximately 60–80% of 1-RM).

Participants assigned to the control group will be provided with the general physical activity recommendations for cancer survivors from the American College of Sports Medicine, which is compatible with health-related physical activity guidelines for the general population, due to ethical reasons, as evidence shows that physical activity during the recovery phase and in cancer survivors is beneficial for the overall health [30]. After completion of the study, the control subjects will be offered mediation to a certified training facility for cancer patients/survivors.

